### Data management

Data for each participant is kept in a Case Record File (CRF), which fulfil the Danish law for medical doctors' obligation to keep patients records. The study personnel involved in the evaluation of clinical outcomes are blinded to the treatment until the data analysis is completed. Blood test results and lists of potential adverse effects are therefore kept separately in a locked safe to which only medical doctors responsible for patient safety and the person involved in the blinding of the study medication have access.

### Safety

#### Safety profile of Epo

Epo is widely used in the treatment of anaemia and generally has a good safety profile. Some potential acute side effects are transient flu-like symptoms, rash at the injection site and headache, which are normally reported as mild and disappear within a few hours. However, long-term Epo-treatment can induce epileptic seizures in medically ill patients with chronic renal failure and past history of seizures [49]. A very rare adverse effect of Epo treatment is a condition where the patient develops neutralising antibodies against Epo resulting in pure red cell aplasia (PRCA). This problem has only been observed in patients treated with subcutaneous injections and was solved in 2003 when the manufacturer changed the preparation, packaging and transport of Epo [50]. Today, Epo-antibody formation is thus an extremely rare condition observed with long-term subcutaneous Epo-treatment of patients with chronic renal failure [51].

Meta-analysis of 5243 renal failure patients in long-term Epo treatment showed a slight increase in mortality (17%; 95% C.I. 1-35%) potentially because of thrombosis at patients' arterial dialysis access site and insufficient treatment of hypertension [52]. Recently, a study of 522 stroke patients treated with Epo vs. placebo also revealed greater mortality in the Epo group, possibly because of interaction with recombinant tissue plasminogen activator (rtPA) used for thrombolysis as well as an unusual low death rate in the placebo group [53].

Weekly high-dose (40,000/48,000 IE) Epo administration to patients with neuropsychiatric disorder increases haematocrit after 5 weeks [20,21] calling for bloodlettings in about 40% of patients when values exceed 50% and 48% for men and women, respectively. However, continued Epo-treatment in the absence of any iron substitution was well tolerated and not associated with further haematocrit increase after 8 weeks of treatment [20,21].

#### Safety precautions

Given the above safety concerns and increased mortality in certain patient groups, the study inclusion and exclusion criteria (see 'Patients and screening') are strictly adhered to and patients' safety monitored closely throughout the study. Given the very low incidence of PRCA, our use of intravenous (vs. subcutaneous) administration and exclusion of patients with renal failure, we believe that the risk of PRCA in the current study is negligible. Nevertheless, reticulocyte counts as first indicator of PRCA will be carefully monitored (see below).

Patients are informed of all potential adverse effects before their inclusion in the study, instructed that iron supplements are strictly prohibited (since they would boost haematocrit levels) and advised to immediately contact their local emergency department if (1) they experience any potential symptoms of thrombosis or (2) their physician suspects PRCA. They are given a pocketsize plastic card with instruction about whom to contact in the event of these symptoms, their contact details, and important information to the medical doctor at the local emergency department.

It is ensured the temperature of the Epo is kept at 2-8°C at all times during transport and storage to avoid damage of the compound and potential associated adverse effects. To minimise the risk of acute allergic reactions, Epo/placebo is dissolved in 100 ml saline and administered as intravenous infusions over 15 minutes. After this, patients' well-being is monitored for at least 30 minutes by a nurse at the clinic in the case of potential transient side effects of Epo like flu symptoms, rash at the infusion site or head ache.

#### Safety parameters and monitoring

Patient safety is monitored with medical examinations, blood pressure measurements, blood tests, ECG and other safety measures at baseline and throughout the study until 2 weeks after cessation of Epo/placebo treatment. For an overview of the safety tests, their frequency and timing see table 1.

If blood tests show significantly increased haematocrit (>50% for men and >48% for women) at two consecutive measurements within a week, bloodletting(s) (450 ml each) will be performed weakly with no cessation of treatment until haematocrit values are normalised. In the case of significant increase in thrombocytes (> 400 billion/L) or drop in reticulocytes (< 1‰) 2 repeated controls will be performed in the following week. If these values remain abnormal, the patient is taken out of the study and monitored with weekly medical examinations and blood tests until the values are normalised or is hospitalised for observation.

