## Methods

### Study design

The present trial has a double-blind, placebo-controlled, parallel-group design in which participants are randomised to receive weekly infusions of either Epo (Eprex; 40,000 IU; Janssen-Cilag) or saline over 8 weeks. Patients complete a broad neurocognitive test battery assessing memory, executive function and attention at baseline, after completion of treatment (week 9) and at follow-up (week 14). Mood, symptoms and quality of life are measured at baseline and weeks 5, 9 and 14 using a variety of rating scales including the Hamilton Depression Rating Scale 17 items (HDRS-17) [1], Young Mania Rating Scale (YMRS) [40], Beck Depression Inventory (BDI) [41], Massachusetts General Hospital Cognitive and Physical Functioning Questionnaire (CPFQ) [42], and the EuroQol visual analogue scale (VAS) for quality of life (EQ-5D) [43]. Patients undergo an fMRI scan at baseline and week 14. Further, plasma and whole blood BDNF and inflammatory markers will be investigated with blood tests at baseline and weeks 5, 9 and 14. Finally, we will assess metabolic parameters with blood tests at baseline and weeks 5, 9 and 14, and body fat mass by Dual energy X-ray absorptiometry (DXA) scanning at baseline and week 9. For an overview of investigations and their timing see table 1.

**Table 1 T1:** Overview of investigations

	Interventions/Assessment domains	Tests/Evaluations	Screening	Baseline & treatment start	Active treatment phase	Treatment-free follow-up period
			
				Week 1	(Week 2-8)	(Week 9-14)
**Treatment**	Investigational drug	EPO (40,000 IU)/Placebo	-	1×	7× (weekly)	-

**Efficacy**	Neurocognitive functions	Neuropsychological testing (120 min)	-	1×	-	2× (week 9,14)
		
		MRI, fMRI and cognitive tests	1×	-	-	1× (week 14)
	
	Psychopathology	Clinical Rating	-	1×	1× (week 5)	2× (week 9,14)
		
		Questionnaires	-	1×	1× (week 5)	2× (week 9,14)
	
	Quality of life questionnaires		-	1×	1× (week 5)	2× (week 9,14)
	
	DXA scan		-	1×	-	1× (week 9)

**Safety**	Physical exam		1×	1×	7× (weekly)	3× (week 9,10,14)
	
	Vital signs		1×	1×	7× (weekly)	3× (week 9,10,14)
	
	Urine pregnancy test		1×	1×	3× (week 3,5,7)	-
	
	ECG		1×	-	2× (week 3,5)	-
	
	Adverse event monitoring		-	* Continuously until week 10*		
	
	Blood analysis	Haematology	1×	1×	7× (weekly)	3× (week 9,10,14)
		
		Blood chemistry	1×	1×	7× (weekly)	3× (week 9,10,14)
		
		BDNF, inflammatory and metabolic markers	-	1×	1× (week 5)	2× (week 9,14)

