### Participants and screening

Patients with treatment-resistant major depression (study 1) and patients with bipolar disorder in full or partial remission but with cognitive problems (study 2) will be recruited through Clinic for Affective Disorders, Department of Psychiatry, Copenhagen University Hospital, Rigshospitalet. The centre receives patients with treatment-resistant major depression or bipolar disorder from the whole Capital Region. Patients will be screened with Schedules for Clinical Assessment in Neuropsychiatry (SCAN) [44] to confirm diagnosis.

Inclusion Criteria are a diagnosis of either treatment-resistant major depression (defined as failure to respond to at least two different types of antidepressants given in sufficient doses over sufficient time) in moderate to severe degree (HDRS score ≥ 17), or bipolar disorder in full or partial remission (HDRS ≤ 14 and YMRS ≤ 14) and subjective experience of moderate to severe cognitive problems on the CPFQ (score ≥ 4 on ≥ 2 domains), age between 18-65 years and unchanged antidepressant or mood stabilising treatment for minimum 2 weeks prior to inclusion in the study.

Exclusion criteria are any significant medical conditions (incl. diabetes, renal failure, epilepsy, untreated hypertension, present or past malignancies and thrombosis), smoking, hypertension, overweight (BMI > 30) or a body weight < 45 or > 95 kg, schizophrenia, present alcohol or substance misuse, acute suicidal risk, present or previous suicide attempts in the past 2 years, pregnancy or breast feeding, contraceptive medication, or a first-degree family history of thromboembolic events or seizure disorders.

A pregnancy test will be performed on female patients in their fertile age before and every second week during the study. Blood screening and physical examinations will be performed at baseline and every week during the treatment period as well as 1, 2 and 6 weeks after treatment cessation to monitor patients' level of red blood cells and ensure patient safety. Written informed consent will be obtained from all patients before their inclusion in the study and letters sent to their general practitioners to avoid any potential medical complications.

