### Further outcome assessments: biomarkers of potential clinical effects

fMRI is performed before and after treatment to investigate the neurophysiological underpinnings for effects of repeated Epo administration on cognitive function and mood. The second fMRI scan is scheduled 6 weeks after treatment cessation (week 14) because hematocrit levels in the two groups should be comparable at this time point [20] and thus not confound data interpretation. We will investigate whether potential memory improvement after Epo vs. placebo administration is associated with increased hippocampal engagement during picture encoding consistent with increased hippocampal BDNF and plasticity [34,38]. The neural correlates of potential improvements in executive function with Epo vs. placebo treatment will be investigated with a spatial N-back working memory test. Finally, we will investigate whether potential antidepressant effects of Epo are accompanied by reduced cognitive and neural response to fearful facial expressions in a face-processing test similar to effects seen with existing antidepressants [32]. This would point to the modulation of emotional bias as a common mechanistically important effect of compounds with diverse neurochemical signalling mechanisms. Structural T1-weighted MRI and diffusion weighted imaging (DWI) at these time points will investigate whether Epo-treatment induces structural changes in the hippocampus and influences functional brain connectivity, respectively. Arterial spin labelling (ASL) will investigate whether Epo introduces enduring changes in global and regional cerebral blood flow (after the return of haematocrit levels to baseline).

It is known that Epo increase hippocampal BDNF and nerve growth factor (NGF) and has anti-inflammatory actions, but it is unclear whether these actions are mechanistically important for potential antidepressant effects of Epo. We will therefore investigate the effect of Epo on plasma and whole blood BDNF, NGF and inflammatory markers incl. interleukin-6 (IL-6) and C-reactive protein (CRP). Given diurnal variation in peripheral BDNF, blood samples are collected at approximately the same time for all patients. For overview of timing see table 1.

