### Limitations

A major limitation of the study design is the implementation of many exclusion criteria (see 'Patients and screening'), which serves to maximise participant safety. This limits the generalizability of the findings to clinical practice. Specifically, our sample may not be particularly representative for the full range of physical and psychiatric comorbidity, response to treatment and functioning of patients seen in the clinic. Nevertheless, this limitation is considered inevitable since patient safety is of principal importance.

From a clinical perspective there are two potential complications of long-term application of Epo to patients with affective disorders. The first problem is the increases in the red cell mass observed with repeated administration leading to increased risk of hypertension and blood clotting [57]. Future studies may wish to assess whether such unwanted haematopoietic activities can be avoided with infrequent Epo administration while maintaining the neuroprotective effects. Another solution could be the use of modified Epo molecules such as carbamylated Epo (CEPO) and asialoerythropoietin (asialoEPO) which have been engineered to have neuroprotective but not haematopoietic actions [58-60]. In the absence of haematological activities, CEPO and asialoEPO exhibit a broad spectrum of neuroprotective activities in models of cerebral ischemia, spinal cord injury and sciatic nerve crush [58,61-63]. These Epo derivatives may thus be promising candidates for long-term treatment of affective disorders.

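### Adverse-event recording stops at week 10 while other safety assessments run to week 14; the protocol's end dates for safety monitoring conflict and leave four follow-up weeks with no stated event recording

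*Protocol article*

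**What the plan says.** All references are to the protocol article.

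- **Study design:** patients are "randomised to receive weekly infusions of either Epo (Eprex; 40,000 IU; Janssen-Cilag) or saline over 8 weeks". Table 1 places one infusion in week 1 and seven in weeks 2 to 8.
- **Table 1, adverse-event row:** "Continuously until week 10".
- **Safety parameters and monitoring:** examinations, blood pressure, blood tests, ECG and "other safety measures at baseline and throughout the study until 2 weeks after cessation of Epo/placebo treatment". The same paragraph sends the reader to Table 1 for timing.
- **Table 1, other safety rows:** physical examination, vital signs, haematology and blood chemistry each have three post-treatment assessments, at weeks 9, 10 and 14.
- **Participants and screening:** blood screening and physical examinations take place weekly during treatment "as well as 1, 2 and 6 weeks after treatment cessation to monitor patients' level of red blood cells and ensure patient safety".
- **Further outcome assessments (biomarkers):** the second fMRI scan is placed at week 14 "because hematocrit levels in the two groups should be comparable at this time point".
- **Limitations:** the first complication named for long-term use is "increases in the red cell mass observed with repeated administration leading to increased risk of hypertension and blood clotting".

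**The concern.** Two things look wrong. First, the end date of examinations, blood pressure measurements and blood tests differs between sections, so site staff cannot tell from the text whether the six-week assessment belongs to safety monitoring. Second, both places that set an end for adverse events choose week 10, although every patient is due back at week 14 and the article uses week 14 as the point at which it relies on the arms having comparable haematocrit.

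What is at stake is completeness of the safety record. The article names clotting and hypertension as the risks that follow from raised red cell mass, and its safety section reports higher mortality under Epo in some other patient groups. A patient with symptoms of thrombosis is told to go to a local emergency department. If that happened in week 12, the patient could be treated elsewhere and, on the stated schedule, nothing would require the event to be entered as an adverse event.

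**Working it through.** **Step 1: calendar.** Table 1 gives 1 + 7 = 8 weekly infusions, so the last is in week 8.

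| Interval after last infusion | Study week |
|---|---|
| 1 week | 8 + 1 = 9 |
| 2 weeks | 8 + 2 = 10 |
| 6 weeks | 8 + 6 = 14 |

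The two-week limit in the safety section and the week-10 limit in the adverse-event row are therefore the same date. The one-, two- and six-week checks under participants and screening match weeks 9, 10 and 14 in the other Table 1 rows.

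**Step 2: end dates side by side.**

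| Item | Safety parameters and monitoring | Participants and screening | Table 1 |
|---|---|---|---|
| Physical examination | week 10 | week 14 | week 14 |
| Blood pressure / vital signs | week 10 | not stated | week 14 |
| Blood tests | week 10 | week 14 | week 14 |
| Adverse events | not named separately | not stated | week 10 |

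The first three rows contradict each other. The fourth is consistent with the safety section, but stops four weeks before the last scheduled safety visit.

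The week-14 assessments cannot be explained as efficacy measurements only. The participants section gives their purpose as following red blood cells and patient safety.

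**Step 3: size of the gap.**

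- Post-treatment follow-up: 14 − 8 = 6 weeks.
- With adverse-event recording: 10 − 8 = 2 weeks, 2/6 = 33%.
- Without: 14 − 10 = 4 weeks, 4/6 = 67%.
- With recording extended to week 14: 6/6 = 100%, with no added visit.

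The schedule is the same in both arms and both studies, so the gap applies to each of the 80 planned patients who stays in follow-up.

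**Step 4: is the mechanism of harm still active after week 10?** The documents do not settle this. The biomarker section says when haematocrit should be comparable, not when it first becomes so. No value is given for weeks 10 to 13. The safety section reports from earlier studies that about 40% of patients needed bloodletting; if that rate applied to the 40 planned Epo patients, it would be 0.40 × 40 = 16. It also reports no further rise after 8 weeks of treatment. Neither figure gives the rate of decline after the last infusion. A raised red cell mass in weeks 11 to 14 is possible and unquantified.

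**Step 5: what a week-14 visit without event recording would catch.** Vital signs and haematology would show hypertension or raised haematocrit still present on that day. They would not show a thrombosis already treated, a hospital admission, or a rise in blood pressure that had settled.

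**The case against.** The strongest reply has four parts.

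1. *A two-week window after the last dose is a design choice, and this is a condensed article.* Reporting windows for serious events may well be in the full protocol. This stands for details that the article leaves out, and for how rates are tabulated by period. It does not cover an end date that the article states twice and that conflicts with another section and with its own table.

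2. *Safety assessment does not stop at week 10.* This is right and limits the point. Week 14 includes examination, vital signs, haematology and chemistry. The gap concerns formal adverse-event recording, chiefly of events between visits.

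3. *Late serious events have other routes.* Patients carry a contact card and emergency instructions, the unblinding procedure for severe reactions has no end date, and patients withdrawn for persistently abnormal thrombocytes or reticulocytes are followed further. These routes reduce the chance that a thrombosis stays unknown to the trial. None of them is a rule for recording adverse events.

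4. *Harm from the gap is not shown.* A reader might infer that haematocrit normalises only at week 14, that events in weeks 11 to 14 would occur mainly under raised red cell mass, and that leaving them out biases the comparison between arms towards no difference. The documents support none of these. The week-14 statement is an expectation made to justify scan timing, and no intermediate values are given. The window is equal in both arms, so a comparison to week 10 remains valid for that period. Any shift towards no difference would depend on how an Epo excess in the later weeks compared with that before week 10, and nothing in the article bears on that.

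**Conclusion.** The point holds as an internal conflict and a gap in recording. The safety section ends examinations, blood pressure and blood tests at week 10, against week 14 in Table 1 and, for examinations and blood tests, in the participants section. Adverse-event recording ends at week 10, leaving 4 of 6 post-treatment weeks uncovered although a week-14 visit exists. The arithmetic rests only on the last infusion being in week 8.

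The clinical weight is uncertain. It depends on whether red cell mass is still raised after week 10, which the article does not report, and on how many events would occur in those weeks, for which it gives no rate. With 80 patients the number of thrombotic events may be very small. It would be wrong to say that late hypertension goes uncounted altogether, or that the safety comparison is biased. The supportable statement is that clinical events occurring or resolving between weeks 10 and 14 have no stated adverse-event recording, in a period when the article itself leaves open whether the named mechanism of harm has ended. The change is worth making because it costs so little.

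**What to change.** 1. Reconcile the sentence under safety parameters and monitoring with the participants section and Table 1, so that one end date is given for examinations, blood pressure and blood tests.
2. Extend the adverse-event row of Table 1 to the existing week-14 visit. At that visit, ask about and record all events since week 10, with a specific question on thromboembolic events and on care received elsewhere.
3. For patients already past week 14, state whether these events will be sought retrospectively, and mark events so obtained. The status section reports 21 randomised by October 2010, so 80 − 21 = 59 planned patients had yet to be randomised at that date and could be covered prospectively.

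The cost is one more adverse-event form per patient at a scheduled visit, plus a short amendment. No visit, sample or treatment rule changes through the added recording.

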#### Procedures for acting on serious adverse effects

Procedures for breaking the randomisation code are established for the case of severe adverse reactions potentially related to the drug intervention. These will be followed when knowledge of the patient's drug treatment will have implications of the treatment of the observed adverse effects. It is the decision of the principal investigator or the medic responsible for safety monitoring to break the emergency envelope for the affected participant.

## Discussion

The present EPO study is the first clinical trial investigating whether repeated administration of Epo is able to improve mood and reverse neurocognitive dysfunction in patients with treatment resistant depression or bipolar illness in remission. In light of the hypothesis that neural plasticity and neurogenesis play a prominent role in the pathophysiology of affective disorders, cognitive function and clinical response to drug treatment, Epo is a compound worth to be considered for future add-on treatment strategies. It is hypothesised that Epo treatment will have antidepressant effects in patients with treatment resistant depression and alleviate the enduring neurocognitive dysfunction in patients with bipolar disorder in remission.

### Current trial status

Patient enrolment started in September 2009 and is ongoing until September 2013. Status in October 2010 is that 21 participants have been screened, enrolled and randomised. One patient has had to drop out after week 5 because of abnormal laboratory results. So far, data sets including all clinical variables and biomarkers are complete for 18 participants.

